#### Patient-centred outcome measures

We will explore the potential for detecting change in each of the following outcome measures for each group separately.

##### Hospital Anxiety and Depression Scale (HADS, [31])

This 14-item scale will be used to assess symptoms of depression (7 items) and anxiety (7 items). This scale has been found to be effective in assessing the symptoms of the severity of anxiety and depression in both secondary and primary care patients [32]. Each item is scored on a scale of 0–3, with 3 indicating higher symptom frequencies. Scores for each subscale (anxiety and depression) range from 0 to 21. A cut-off score of at least 8 for each subscale will be used as an indication of caseness of depression and/or anxiety. HADS is likely to be the primary outcome in the main trial.

##### Brief Pain Inventory (BPI, [33])

Pain severity/intensity as well as pain interference with daily life will be assessed with this numerical rating scale (scaled from 0 to 10). This scale assesses the average pain, which is associated with PD according to the patient’s point of view. Thereby, 0 represents no pain and 10 the most painful sensation imaginable.

##### Fatigue Severity Scale (FSS, [34])

This nine-item scale will be used to assess the impact of fatigue on the daily living of patients. It comprises three items related to physical impact, three items to the psychological environment, and the remaining three are more generic. Each item is rated on a 7-point Likert scale (1 = completely disagree–7 = completely agree). Mean scores of 4 or more define significant fatigue.

##### Insomnia Severity Index (ISI, [35])

This self-report measure consists of seven items that assess the nature, severity, and impact of insomnia in the last 2 weeks. Each item is rated on a 5-point Likert scale (0 = not at all–4 = extremely) with total scores ranging from 0 to 28, whereby higher scores indicate greater insomnia severity.

##### Parkinson’s Disease Activities of Daily Living Scale (PADLS, [36])

This self-report scale will assess difficulties in daily activities due to PD. This five-item scale provides a single global rating of how patients perceive their illness, with higher scores indicating greater difficulty in activities of daily living.

#### Process mechanism measures

We will also assess some mindfulness-related mechanisms. Participants will be asked to keep a diary in which they will monitor the frequency and duration of their home mindfulness practice.

##### Self-Compassion Scale—Short Form (SCS-SF, [37])

Research has shown that self-compassion is associated with psychological well-being and suggests that self-compassion might be an important protective factor, fostering emotional resilience (see Neff, [39], for a review). Self-compassion will be assessed using 12 items and a total score will be generated. This short form of the SCS demonstrates adequate internal consistency (Cronbach’s alpha ≥ 0.86) and a near-perfect correlation with the long form SCS (*r* ≥ 0.97) [37].

##### Experiences Questionnaire (EQ, [40])

This questionnaire measures decentering, one of the process mechanisms that are used during the MBI course with the view to reduce distress. Decentering is defined as the ability to observe one’s thoughts and feelings as temporary, objective events in the mind, as opposed to reflections of the self that are necessarily true. An initial validation study of EQ showed that levels of decentering among people with major depression were significantly and negatively correlated with concurrent self-report (*r* = −0.46) and clinician-assessed (*r* = −0.31) levels of depression symptoms.

##### Acceptance Action Questionnaire (AAQ-II, [41])

The AAQ-II assesses acceptance, experiential avoidance, and psychological inflexibility, which is related to a range of outcome, from mental health to work absence rates. Results from 2816 participants across six samples indicate the satisfactory structure, reliability, and validity of this measure [42].

##### Philadelphia Mindfulness Scale (PHLMS, [43])

This 20-item scale comprises two subscales: awareness and acceptance. The awareness subscale assesses noticing and being aware of thoughts, felons, perceptions, and body sensations, while the acceptance subscale assesses experiential avoidance.

##### Intolerance of Uncertainty Scale—Short Version (IUS-12, [44])

The 12-item scale measures the participant’s response to uncertainty, ambiguous situations, and the future. It is rated on a 5-point Likert scale ranging from 1 (not at all characteristic of me) to 5 (entirely characteristic of me).

##### Home practice diary

Participants will be asked to keep a diary (either on paper or online) in which they will monitor the frequency and the duration of their home mindfulness practice.

#### Health economics measures

Participants of both arms will be measured using the assessments described below.

##### Subjective well-being (SWB, [45])

These four items from the Office of National Integrated Household Survey, 2011, will assess feelings regarding participants’ life satisfaction, happiness, anxiety, and life as something worthwhile at baseline, pre-, and post-intervention time points.

##### EuroQol five-dimensional questionnaire and visual analog scale (EQ-5D-3L and EQ-VAS, [46, 47])

The EQ-5D-3L is a five-item composite measure, and the EQ-VAS is a visual analog scale, both developed by the EuroQol Group. The EQ-5D-3L consists of five dimensions (mobility, self-care, usual activities, pain/discomfort, and anxiety/depression) each with three levels of problems. Both the EQ-5D-3L and EQ-VAS will be used to assess participants’ quality of life.

##### The ICEpop CAPability measure for Adults (ICECAP-A, [48]) and the Adult Social Care Outcomes Toolkit (ASCOT, [49])

The ICECAP-A is a measure of capability for the general adult population (+18) comprised of five attributes of well-being (attachment, stability, achievement, enjoyment, and autonomy); the ASCOT is a self-compliance questionnaire comprised of eight attributes (personal cleanliness and comfort, food and drink, control over daily life, personal safety, accommodation cleanliness and comfort, social participation and involvement, occupation, and dignity).

#### Feedback interview procedure

At the end of the 8-week intervention period, participants, in the MBI group, will also be included to be interviewed by an MSc health psychology student who has not had any involvement in other aspects of the trial. Participants will be asked to give open and honest accounts of their experiences and opinions of the intervention (see topic guide, Table 3). Questions address expectations regarding the intervention, experiences of MBI sessions, features of the intervention liked and disliked, and the process of change (or not) as a result of the course. Each interview will be digitally recorded. Interviews will be anonymised and transcribed; any information that may compromise confidentiality will be omitted before the transcripts come to the research team.

**Table 2 Tab2:** Details and schedule of the MindPD trial assessment procedure

Assessments administered	Screening (week 0)	Baseline (week 1)	Mid-intervention (week 4)	Post-intervention (week 8)	3-month follow-up (week 20)
Main details sheet	X				
Telephone Interview for Cognitive Status Instrument modified version (TICS-M)	X				
Demographics sheet		X			
Primary outcome measure:					
Hospital Anxiety and Depression Scale (HADS)		X	X	X	X
Secondary outcome measures:					
Parkinson’s Disease Activities of Daily Living Scale (PADLS)		X	X	X	X
Brief Pain Inventory (BPI)		X	X	X	X
Fatigue Severity Scale (FSS)		X	X	X	X
Insomnia Severity Index (ISI)		X	X	X	X
Process variables:					
Self-Compassion Scale (SCS)		X	X	X	X
Philadelphia Mindfulness Scale (PHLMS)		X	X	X	X
Experiences Questionnaire (EQ)		X	X	X	X
Acceptance Action Questionnaire (AAQ-II)		X	X	X	X
Intolerance of Uncertainty Scale (IUS-12)		X	X	X	X
Health economics variables:					
Subjective Well-Being questionnaire (SWB)		X		X	X
EuroQoL and visual analog scale (EQ-5D-3L and VAS)		X		X	X
ICEpop CAPability Measure for Adults (ICECAP-A)		X		X	X
Adult Social Care Outcomes Toolkit (ASCOT)		X		X	X
Home practice				X	X

### Data protection and confidentiality

Recordings, transcripts, and documentation relating to participants will be stored in a locked filing cabinet at PI’s office at City, University of London and only available to the research team. Each participant will be assigned a study ID that will be kept separate to a list with ID and names. Data stored on the computer will be password protected, and only members of the research team will know the password. In the write-up of the research, names and any other identifiable information will not be used.

### Blinding

The research trial coordinator will coordinate all assessment procedures. Data will be downloaded in an Excel spreadsheet by the trial coordinator. All assessments are based on self-report online assessments, rather than rated or imputing by a member of the research team. Therefore, influences of observer biases are not expected.

Due to the nature of the intervention, it is not possible to blind the principal investigator, as she will be delivering the MBI sessions. It is also not possible to blind participants to intervention allocation. During statistical analysis, the intervention groups will be assigned a code rather than their name (i.e. WLC vs. MBI) so that the researchers are unaware of what the intervention group code represents.

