#### Booking in participants’ groups

On receiving the randomisation outcome from the research trial coordinator, the first author will contact the participants to notify them of their group allocation. Participants in the MBI group will be offered a date for their first session. Participants in the WLC group will be discouraged from any new mindfulness-related activities during the trial.

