#### Missed sessions and homework

AB will record attendance and make notes on participation. Details of issues covered and homework engagement will be recorded as well. In the case of non-attendance at sessions, AB will contact the participant to ascertain the problem and to discuss a suitable solution addressing any concerns. Unfortunately, because of the group setting of this intervention, participants will not have the opportunity to reschedule a missed session.

Participants will be asked to keep a diary (provided with the manual) of their weekly homework mindfulness practices. A record of homework engagement will be kept, and final analyses will control for homework compliance.

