#### Withdrawals from MBI course

If a participant expresses the wish to withdraw from the MBI course, AB will contact the participant to ascertain the reason for drop-out if the participant is willing to share this.

The reason for withdrawal (e.g. adverse events, illness progression, inability to adhere, inability to attend) will be discussed with all team members, and the information will be recorded as appropriate. Again, if it is felt that a participant should be withdrawn from the course, this will be discussed in a meeting with all the members of the research team.

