### Data analysis plan

#### Quantitative analysis plan

Statistical analysis will be carried out in STATA. Descriptive statistics (mean, median, standard deviation) will be calculated for all demographics and clinical variables. All group comparisons will be carried out on an intention-to-treat basis, that is participants will be analysed in the group to which they were randomised. Descriptive results concerning recruitment numbers, completions, drop-out rates, and missing data will be calculated and reported. The quantitative data will be summarised with standard descriptive measures for each group separately to determine potential change within group over time. Continuous variables will be summarised by their mean and standard deviation, categorical variables as numbers and percentages, and presented with 95% confidence intervals. With the aim of identifying a potential response shift in some of the participants, a retrospective measurement will also be implemented. In particular, then-test questions will be added to the post-intervention and 20-week follow-up questionnaires for several outcome variables. Both measurements of the effect of the course (prospective and retrospective) will be compared, in order to add robustness to the results. We will also assess the sensitivity of the results to excluding patients who did not receive a sufficient number of MBI sessions or those who had little meditation home practice.

**Table 3 Tab3:** Topic guide for participants’ experiences with the mindfulness course

Questions	Prompts
1. First of all, can you start by telling me what you were expecting from the mindfulness sessions?	-What did you think the programme would be like? -In what ways (if any) did you think it might help you?
2. How did you find the programme overall?	-Tell me how you found your first session -Tell me about the other sessions -Tell me how you found the homework tasks
3. Can you tell me what you liked about the programme?	-What was helpful? Why? How? -Were there some sessions/some aspects that were more helpful than others?
4. Can you tell me what you disliked about the programme?	-What was unhelpful? Why? How? -Were there some sessions/some aspects that were less helpful than others?

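### The claim that coded arms keep the analysis blind has no limit, yet it cannot be true for the compliance, exposure and intraclass-correlation analyses, and it is unprotected for the intention-to-treat comparisons

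*Protocol article*

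**What the plan says.** All of this is in the protocol article.

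- **Blinding.** The section makes the promise: "During statistical analysis, the intervention groups will be assigned a code rather than their name", "so that the researchers are unaware of what the intervention group code represents". It names no subset of analyses and no order of unblinding. It concedes that "it is not possible to blind the principal investigator, as she will be delivering the MBI sessions", and that participants cannot be blinded either. The trial coordinator downloads the data into a spreadsheet.
- **Booking in participants' groups.** The principal investigator contacts participants "On receiving the randomisation outcome from the research trial coordinator", so the coordinator also knows the allocation.
- **Missed sessions and homework.** The facilitator will "record attendance and make notes on participation". A practice diary comes with the course manual. The section then commits to an adjustment: "A record of homework engagement will be kept, and final analyses will control for homework compliance".
- **Quantitative analysis plan.** Group comparisons follow intention to treat. A sensitivity analysis looks at the effect of "excluding patients who did not receive a sufficient number of MBI sessions or those who had little meditation home practice".
- **Study sample.** Six intervention groups are planned so that intraclass correlations can be estimated.
- **Withdrawals from MBI course.** The reason for leaving the course "will be discussed with all team members".

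**The concern.** Coding the arms conceals allocation only if nothing else in the analyst's file reveals it. A variable that is filled in for one arm and empty for the other reveals the code as surely as a label would. The plan promises concealment for statistical analysis as a whole and also commits to analyses that need such variables.

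What is at stake is modest but real. Participants and the principal investigator are unblinded and the outcomes are self-reported, so coded analysis is one of the protections the plan claims. If the final report repeats the claim without limit, readers will credit blinding to results that did not have it. If the revealing data travel with the outcome scores, the main comparisons lose a protection they could have kept.

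**Working it through.** This is a check of consistency between sections, with a little arithmetic.

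**Step 1: the plan's own figures.** There are 60 participants, 30 per arm (Design and theoretical framework). Course groups have five people (Mindfulness-based intervention for PD). 30 / 5 = 6 intervention groups, as stated under Study sample. All six come from the MBI arm; the wait-list arm has no session groups.

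**Step 2: which arm has the data.**

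| Variable | Source | MBI | Wait-list before week 20 |
|---|---|---|---|
| Sessions attended | Facilitator's record | up to 30 of 30 | 0 of 30 (no sessions) |
| Home-practice diary | Supplied with the manual, which is issued before the first session | up to 30 of 30 | 0 of 30 (no manual) |
| Session group | Course groups of five | 30 of 30 | 0 of 30 |

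Wait-list participants are offered the course only once the 20-week follow-up is over (Wait-list control group), and until then they are discouraged from taking up mindfulness (Booking in participants' groups).

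**Step 3: where the plan uses these data.**

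1. Homework compliance, as an adjustment in the final analyses.
2. Sessions and home practice, as grounds for exclusion in a sensitivity analysis.
3. Session group, for the intraclass correlation.

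**Step 4: what the code then conceals.** The code has two values. One filled-in attendance, diary or session-group field under one value identifies that arm, and with it the allocation of all 60 participants. In each of the three uses in Step 3 the analyst must hold such a field, so the code conceals nothing.

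**Step 5: the intention-to-treat comparisons.** These need baseline and outcome scores and a coded arm, and no variable from Step 2. They can be run blind. Two statements leave that unprotected: the compliance adjustment is attached to the final analyses and not to a secondary set, and Table 2 lists home practice at weeks 8 and 20 in the same schedule as the outcome scales.

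**Step 6: who could be blind.** The principal investigator delivers the course. The coordinator relays allocation and downloads the data. The claim can therefore apply only to an analyst separate from both.

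**The case against.** **The intention-to-treat comparisons can be blinded, and file layout belongs in a full protocol or SAP.** Both parts stand. A reader might infer that coding must fail for the whole analysis. The documents do not support that: no section describes a single merged file, and nothing rules out a staged release. The absence of a data-cut specification is not the finding. The finding is that the article states a property without limit which its own planned analyses contradict.

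**The one-arm reading is inferred.** Partly true. The Home practice row of Table 2 and the diary descriptions under Process mechanism measures do not name an arm. The reading rests on the diary coming with the manual and on the wait-list arm having no course until after follow-up. Even if wait-list participants were asked about practice, current meditators are excluded and new practice is discouraged, so values near zero would be expected and would still point to the arm. Session counts and session groups do not depend on this inference.

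**Exposure analyses are arm-aware by nature, so nothing is lost.** They are, which is why the claim should not cover them. A reader might go further and infer that analytic choices would be made unblinded. That does not follow: the cut-offs for enough sessions or little practice may be fixed in a document not shown.

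**The withdrawal discussions break the code.** A reader might infer this too. The article does not say that an analyst attends, or that a withdrawal could be linked to a coded record; study IDs are kept apart from names (Data protection and confidentiality). These discussions are a route to guard against and not evidence of unblinding.

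**Conclusion.** The point holds in limited form. The unrestricted blinding claim is untrue for three planned uses of the data: the compliance adjustment, the exclusion by sessions or practice, and the intraclass correlation. For the intention-to-treat comparisons, blinding is possible but unprotected as the article is written.

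The size can be stated only as certainty of identification: any one of the three variables reveals the arm. The documents give no basis for a figure of bias. A reader might count the follow-up contrasts in Table 2, with one score per instrument: 10 instruments × 3 follow-ups + 4 × 2 = 38, and 38 × 0.05 = 1.9 intervals excluding zero by chance. That number describes multiplicity, would be the same with a fully blinded analyst, and should not be cited as the size of this problem.

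The verdict assumes that the manual, and with it the diary, goes only to course participants before week 20, and that the researchers to be kept blind include an analyst other than the principal investigator and the coordinator.

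**What to change.** 1. Limit the statement under Blinding to the intention-to-treat comparisons.
2. Have the coordinator first release a file with baseline scores, outcome scores and a coded arm only, with no attendance, diary or session-group data. Run the intention-to-treat comparisons on it and file them.
3. Then merge the adherence and session-group data, and report the compliance, exclusion and intraclass-correlation analyses as unblinded.
4. Keep the analyst out of the withdrawal discussions until step 2 is filed.
5. Do not give wait-list participants artificial clusters, such as their randomisation block, to disguise the arm. They are not treated in groups, and invented clusters would impose a structure that arm does not have.

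If the staged release is not wanted, delete the blinding claim. The cost is protocol wording and one extra data cut by the existing coordinator, with no new staff.

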### Compliance

This pilot trial will be conducted in compliance with the Declaration of Helsinki, Medical Research Council Good Clinical Practice (GCP) guidance, the Data Protection Act (1998), the National Research Ethics Service (NRES) approvals, National Health Service (NHS) Trust regulations, and other regulatory requirements as appropriate. The final trial publication will include the items recommended under the CONSORT statement for randomised trials [50].

### Participant safety

This MBI course is expected to be of low risk to participants. Mindfulness approaches are non-invasive and have been previously used successfully in chronic illness populations [14]. If AB is concerned about a patient’s safety, a referral will be made to ensure the participant gets the support he/she needs.

#### Withdrawals from MBI course

If a participant expresses the wish to withdraw from the MBI course, AB will contact the participant to ascertain the reason for drop-out if the participant is willing to share this.

The reason for withdrawal (e.g. adverse events, illness progression, inability to adhere, inability to attend) will be discussed with all team members, and the information will be recorded as appropriate. Again, if it is felt that a participant should be withdrawn from the course, this will be discussed in a meeting with all the members of the research team.

### Data analysis plan

#### Quantitative analysis plan

Statistical analysis will be carried out in STATA. Descriptive statistics (mean, median, standard deviation) will be calculated for all demographics and clinical variables. All group comparisons will be carried out on an intention-to-treat basis, that is participants will be analysed in the group to which they were randomised. Descriptive results concerning recruitment numbers, completions, drop-out rates, and missing data will be calculated and reported. The quantitative data will be summarised with standard descriptive measures for each group separately to determine potential change within group over time. Continuous variables will be summarised by their mean and standard deviation, categorical variables as numbers and percentages, and presented with 95% confidence intervals. With the aim of identifying a potential response shift in some of the participants, a retrospective measurement will also be implemented. In particular, then-test questions will be added to the post-intervention and 20-week follow-up questionnaires for several outcome variables. Both measurements of the effect of the course (prospective and retrospective) will be compared, in order to add robustness to the results. We will also assess the sensitivity of the results to excluding patients who did not receive a sufficient number of MBI sessions or those who had little meditation home practice.

**Table 3 Tab3:** Topic guide for participants’ experiences with the mindfulness course

Questions	Prompts
1. First of all, can you start by telling me what you were expecting from the mindfulness sessions?	-What did you think the programme would be like? -In what ways (if any) did you think it might help you?
2. How did you find the programme overall?	-Tell me how you found your first session -Tell me about the other sessions -Tell me how you found the homework tasks
3. Can you tell me what you liked about the programme?	-What was helpful? Why? How? -Were there some sessions/some aspects that were more helpful than others?
4. Can you tell me what you disliked about the programme?	-What was unhelpful? Why? How? -Were there some sessions/some aspects that were less helpful than others?
5. Tell me about anything that you feel has changed from having done the programme?	-Can you tell me what changed? (Anything different in your day-to-day life, the way you are dealing with PD?) -Can you tell me how you came to notice things changing? -Why/how do you think things changed?
6. Do you have anything else you would like to tell me about your experiences of this programme that have not already covered?	-What would you feed back to the people who put together the programme? -What advice would you give to people thinking about taking part in mindfulness-based programmes?
7. What do you think of the questionnaires used and the overall set-up of the study?	-How did you find participating in a course over Skype? -Any further comments regarding the questionnaires used?

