### Aims

The overall objective of this study is to assess the feasibility of procedures and processes as well as potential efficacy (i.e. explore potential for detecting change in each of the proposed measures for each group) of a mindfulness-based intervention (MBI) for people with PD, which will be delivered via Skype.

The specific aims of this trial are to:Monitor rates of recruitment, retention, refusal, adherence to the mindfulness sessions, and homework practice, as well as the appropriateness of eligibility criteria to determine the rate of each for planning the main trialAssessing time and resource problems, for example whether it is feasible for patients to answer all the questionnaires and the time taken to do so, the flow of participants entering the study, the use of equipment to set up Skype, and other resources neededDetermine data management issues, by monitoring levels of missing data and data variabilityEvaluate the potential for detecting a change in each of the proposed outcome measures (anxiety, depression, pain, fatigue, insomnia, quality of life, subjective well-being, physical impact of PD, health costs) when comparing the mindfulness-based intervention (MBI) group to the wait-list control (WLC) groupUnderstand the mechanisms of change (mindfulness skills, acceptance, self-compassion, decentering, tolerance of uncertainty) in each patient group, including any potential nocebo effects in the WLC groupAssess the qualitative experiences of receiving the mindfulness intervention and people’s views and experiences of using Skype as a mode of delivery as well as people’s feedback on the questionnaires used

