## Methods/Design

### Design and theoretical framework

We will use a parallel group randomised controlled design. A total of 60 participants with PD will be randomly assigned to either an 8-week MBI course (*n* = 30) or a WLC (*n* = 30). CONSORT flow chart of the study is summarised in Fig. 1.

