### Participants

#### Study sample

A pilot phase II trial of at least 30 participants is considered adequate for obtaining reasonably reliable sample size estimates [24]. We aim to recruit 60 people affected by PD. This sample will allow us to include six intervention groups to estimate intraclass correlations that relate to the fact that we are treating people in groups rather than individually.

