#### Economic evaluation plan

Cost comparisons will be made between the mindfulness course and the standard care. Service cost data will be combined with the primary outcome measures (HADS) and quality-of-life measures generated from the EQ-5D-3L to assess cost-effectiveness. If the intervention has lower costs and better outcomes, then it will be ‘dominant’. In the event of the intervention having higher service costs and better outcomes, cost-effectiveness will be assessed using incremental cost-effectiveness ratios. To address uncertainty in cost and outcome differences, we will run different sensitivity analyses, as tornado diagrams, worst-best scenarios or cost-effectiveness acceptability curves. The results of this economic evaluation should be treated with caution as the study is underpowered. However, the results will give an indication of the potential cost-effectiveness of the mindfulness intervention.

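### The fourth aim compares the mindfulness course with wait-list, but the only clinical-outcome analysis described is change within each arm; no between-arm contrast is defined

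*Protocol article*

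**What the plan says.** The protocol article frames the efficacy question in two ways.

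- **Comparative.** The fourth specific aim under Aims is to evaluate the potential for detecting change in the listed outcomes when MBI is compared with WLC.
- **Arm by arm.** The overall objective, in the same section, glosses potential efficacy as: "explore potential for detecting change in each of the proposed measures for each group". Patient-centred outcome measures says: "We will explore the potential for detecting change in each of the following outcome measures for each group separately". The Quantitative analysis plan says: "The quantitative data will be summarised with standard descriptive measures for each group separately to determine potential change within group over time".

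The Quantitative analysis plan also compares prospective change with retrospective (then-test) change, and describes both as measuring the course's effect.

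Two places point to a comparison of arms. The Quantitative analysis plan states: "All group comparisons will be carried out on an intention-to-treat basis, that is participants will be analysed in the group to which they were randomised". The Economic evaluation plan states: "Cost comparisons will be made between the mindfulness course and the standard care". It adds that, if the intervention costs more and does better, "cost-effectiveness will be assessed using incremental cost-effectiveness ratios", with HADS and EQ-5D-3L as the outcomes.

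**The concern.** A change score within one arm contains the effect of the course, if there is one, plus regression to the mean, the natural course of the disease, the effect of repeated questionnaires, and expectation. The randomised wait-list arm is there to separate these, and it does so only when the two arms are contrasted directly. Noting that one arm changed and the other did not is not that contrast.

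This bears on a decision. The Discussion says that a grant for a large trial will be prepared if the intervention is feasible and potentially effective. If that second judgement is formed from separate within-arm summaries, it can come out favourable with no difference between arms. The Discussion also warns that a wait-list can produce nocebo effects, which makes it more important to report the between-arm estimate and the WLC course side by side and keep them distinct.

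**Working it through.** **1. Is a between-arm contrast defined anywhere?**

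| Place in the protocol article | What it fixes |
|---|---|
| Aims, fourth specific aim | MBI compared with WLC |
| Aims, overall objective | Change for each group |
| Patient-centred outcome measures | Change for each group separately |
| Quantitative analysis plan, outcome summaries | Descriptive change within group over time |
| Quantitative analysis plan, intention-to-treat sentence | Who is analysed in which arm; no contrast, time point or interval for a difference |
| Economic evaluation plan | Incremental ratios, which need an outcome difference between arms |

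The intention-to-treat sentence defines an analysis set, not an estimate. The incremental ratio has a between-arm outcome difference as its denominator, so the economic plan relies on a HADS difference that the quantitative plan does not define.

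**2. The design figures.** "A total of 60 participants with PD will be randomly assigned to either an 8-week MBI course", with 30 per arm. Six blocks of 10 give 6 × 10 = 60, and six session groups of five give 6 × 5 = 30 in the MBI arm; both agree. The sample size rests on a rule of thumb ("A pilot phase II trial of at least 30 participants is considered adequate for obtaining reasonably reliable sample size estimates") with no alpha, power, SD or effect size, so there is no power calculation to reproduce.

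**3. How misleading could separate within-arm readings be?** The change d and correlation r below are assumptions; the protocol gives neither. Both arms improve by the same d (in SD units), so the true difference is zero.

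- Standard error of mean change: √(2(1−r)) / √30. For r = 0.5 this is 1/√30 = 0.183; for r = 0.7 it is 0.775/√30 = 0.141.
- p = probability that one arm's 95% interval for change excludes zero (normal approximation) = Φ(d/SE − 1.96) + Φ(−d/SE − 1.96).
- Exactly one arm excludes zero: 2p(1−p). MBI alone: p(1−p).

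| r | d | p | Exactly one arm | MBI alone |
|---|---|---|---|---|
| 0.5 | 0.2 | 0.195 | 0.31 | 0.16 |
| 0.5 | 0.3 | 0.376 | 0.47 | 0.23 |
| 0.5 | 0.4 | 0.591 | 0.48 | 0.24 |
| 0.5 | 0.5 | 0.782 | 0.34 | 0.17 |
| 0.7 | 0.2 | 0.293 | 0.41 | 0.21 |
| 0.7 | 0.3 | 0.564 | 0.49 | 0.25 |
| 0.7 | 0.4 | 0.807 | 0.31 | 0.16 |
| 0.7 | 0.5 | 0.942 | 0.11 | 0.05 |
| either | 0 | 0.050 | 0.095 | 0.05 |

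Over d = 0.2 to 0.5, exactly one arm runs from 0.11 to 0.49. With the t distribution it is 0.14 to 0.50. The ceiling of 2p(1−p) is 0.50, so the upper end is the worst case.

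**4. What a direct comparison would deliver.** Half-width of the 95% interval for the between-arm difference, in SD units: 1.96 × √((2/n)(1−r²)), with r the assumed correlation of baseline with outcome.

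| n per arm | Unadjusted | r = 0.5 | r = 0.7 |
|---|---|---|---|
| 30 | 0.51 | 0.44 | 0.36 |
| 24 (assumed 20% loss) | 0.57 | 0.49 | 0.40 |

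Clustering in MBI session groups of five, with an assumed intraclass correlation of 0.05 to 0.10, gives a design effect of 1 + 4 × 0.05 = 1.2 to 1 + 4 × 0.10 = 1.4 in that arm. The unadjusted half-width at n = 30 becomes 1.96 × √(1.2/30 + 1/30) = 0.53 to 1.96 × √(1.4/30 + 1/30) = 0.55.

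Unadjusted two-sided power at 0.05 with 30 per arm is about 21%, 49% and 87% for differences of 0.3, 0.5 and 0.8 SD. An estimate with an interval is informative; a test would be underpowered for moderate effects.

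**The case against.** The best defence has four parts.

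- **The arms are compared somewhere.** Intention-to-treat group comparisons are announced, the Blinding section has arms coded for the analysis, and incremental ratios need outcome differences. This stands. A reader might infer that the randomised control is never used; the document does not support that.
- **Within-arm summaries have a purpose.** The fifth aim asks about mechanisms in each group and nocebo effects in WLC, and the Discussion promises to report any WLC worsening. Descriptive reporting is also normal in a pilot. This stands too: the summaries should stay, and the lack of hypothesis tests is not a fault.
- **Detail belongs in the full protocol or SAP.** This is right for covariates, model form and missing-data handling, none of which is held against the article. It does not answer the conflict, because the article itself says three times that change is looked at by group, against its own comparative aim.
- **The illustration uses a rule that the protocol does not contain.** Correct. Nothing says that an arm will be judged by whether its interval excludes zero, and the intervals are attached to summaries rather than explicitly to change scores. The percentages show how far within-arm readings can diverge by chance; they are not an error rate of this trial.

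A reader might also infer that baseline scores are wasted. They are not: change over time is computed from them. They are simply not named as a covariate.

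**Conclusion.** The conflict is in the text and needs no assumption: followed as written, the clinical-outcome analysis does not answer the fourth aim, and describing within-person change as the course's effect adds to the problem. The roughly 10% to 50% range depends on the assumed equal improvement, correlation and 30 analysed per arm, and is illustrative only.

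Severity is moderate. This is a pilot, its consequence is a grant application for a larger trial with an active control, feasibility must be met as well, and the authors call the economic evaluation underpowered and warn of nocebo inflation themselves.

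**What to change.** Reconcile Aims, Patient-centred outcome measures and the Quantitative analysis plan as follows.

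- For HADS anxiety, HADS depression and the other outcomes, state that the between-arm mean difference at weeks 8 and 20 will be estimated with a 95% confidence interval, without hypothesis tests.
- Adjust for the baseline score, which is already collected, and allow for MBI session groups, whose intraclass correlation the Study sample section already sets out to estimate.
- Keep the within-arm summaries as description, including any worsening in WLC, and stop calling within-person change the effect of the course.
- Use the same between-arm HADS and EQ-5D-3L differences in the economic evaluation.

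The cost is a few sentences and one standard Stata model per outcome, with no extra data or participants.
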